**Figure 1 figure1:**
[figure not shown]
Cochlear implant home care (CHOICE) web app patient dashboard.

### Participants

#### Overview

The following 7 UK centers will offer CHOICE to their patients:

St Thomas’ Hospital Hearing Implant Center, LondonUniversity of Southampton Auditory Implant ServiceRoyal National Throat Nose and Ear Hospital, LondonNottingham Auditory Implant ProgramNorth East Regional Cochlear Implant Program, MiddlesbroughThe Richard Ramsden Center for Hearing Implants, ManchesterEmmeline Center, Cambridge

All adult sites were contacted about CHOICE and its evaluation; these sites wanted to be involved. CHOICE is currently an intervention for adults only. Initially, scaling up to only 7 of the adult sites will allow for detailed evaluation. Depending on the evaluation results, CHOICE may be offered to all sites in the future.

#### Proposed Sample Size

We do not yet know what proportion of patients will choose to follow this pathway, as the previous study was a single-center randomized controlled trial involving a limited number of patients [10]. However, 7 centers care for approximately one-third of the approximately 12,000 adults [28] with cochlear implants in the United Kingdom. At the early stages of project planning, we estimated that if 40% of patients enrolled, this may involve approximately 1700 patients. We expect this to be the upper limit for recruitment. Scaling up a digital health tool for people with cochlear implants has not been done before; thus, we cannot predict the uptake. We anticipate that up to 10 members of staff per will be involved per site (total 70). As the aim of the project was not to formally test a hypothesis, a sample size calculation was not conducted.

#### Recruitment

We recommend shared decision-making among the patient, their family, and their clinician to decide who should be on a remote care pathway [29]. Factors that need to be considered include the patient’s care needs; routine maintenance of equipment; access to technology; mobility; literacy; dexterity; any comorbidities (eg, visual impairment); and other factors, such as do they live alone and do they have transport. All patients who meet the inclusion criteria and, after discussing with their clinician as needed, choose the remote care pathway will be invited to participate in the study. Only those who consent to the study will be able to continue with remote care at this stage. As patients’ circumstances and abilities change, we recommend service delivery flexibility, with easy transfer to a clinic-based care model, if required. Staff at participating centers will be invited to take part and sign a consent form for their data to be included in the evaluation. Participant recruitment commenced on June 11**,** 2019, and continued until January 31, 2021.

#### Patient Inclusion Criteria

The inclusion criteria for patients are as follows:

Using a cochlear implant (any device—unilateral or bilateral)Living in the United KingdomAged ≥18 yearsAble to give informed consent to data sharingAccess to a computer or device with internet accessWilling and able to comply with CHOICE pathwayWilling and able to comply with the evaluation

#### Health Professional Inclusion Criterion

The inclusion criterion for health professionals was being a staff member at participating cochlear implant centers.

### Evaluation and Research Outcomes

#### Overview

The Wessex Academic Health Science Network (AHSN) will perform an independent evaluation to assess the impact and success of the care pathway on patients, staff, and services and understand the process of implementing CHOICE using a concurrent triangulation mixed methods design. It will be both an outcome and process evaluation. The evaluation was commissioned in September 2017 and is informed by a growing research base on the challenges associated with the adoption and spread of digital programs. The research team will collect the clinical outcome measures. All the outcomes, methods, and measures corresponding to the research questions are listed in Table 1.

**Table 1 table1:** Outcomes, methods, and measures collected from patients, staff, and services.

Outcome			Research question		Method		Measures		Time point
**Patients**									
	Patient impact (engagement)	1		Quantitative		CHOICE^a^ web app data: number of log-ins, time spent on CHOICE, uses of self–device adjustment (if appropriate), and uses of home hearing check		All data	
	Patient impact (quality)	1		Quantitative		Number of errors in CHOICE, adverse events, and missed issues		All data	
	Patient impact	1		Quantitative		Survey about use of follow-up care (consequences for travel cost, time, hours off work, and child care [including accompanying person])		Once at patient focus group or interview	
	Patient impact	1		Quantitative		NHS^b^ Friends and Family Test		Minimum of twice: baseline (on registration) and after using CHOICE for several months	
	Patient impact	1		Qualitative		Focus groups		Once: planned but unable to happen because of the COVID-19 pandemic	
	Patient impact	1		Qualitative		One-on-one interviews		Once: for patients who prefer one-on-one interviews or if focus groups cannot occur; toward the end of the project	
	Patient empowerment	2		Quantitative		PAM^c^ questionnaire and CI-EMP^d^ questionnaire		Baseline (on registration) and 6 months following registration or end of the project—whichever comes sooner	
	Patient hearing	2		Quantitative		Home hearing check results		All data	
	Patient change in empowerment, hearing, and quality of life	2		Quantitative		Global ratings of change questionnaire		Baseline (on registration) and 6 months following registration or end of the project—whichever comes sooner	
	Patient health-related quality of life, including hearing	2		Quantitative		HUI3^e^ questionnaire		Baseline (on registration) and 6 months following registration or end of the project—whichever comes sooner	
	Patient health-related quality of life	2		Quantitative		EQ-5D-5L^f^ questionnaire		Baseline (on registration) and 6 months following registration or end of the project—whichever comes sooner	
	Patient preference of service delivery	2		Quantitative		Discrete Choice Experiment questionnaire		Baseline (on registration) and 6 months following registration or end of the project—whichever comes sooner	
	Patient confidence and experience	4 and 5		Quantitative		R-Outcomes surveys		Baseline (on registration) and every 6 months; some participants may choose to complete an optional, shorter questions set more often	

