## Methods

### Project Design and Setting

This is a prospective, interventional, multisite, quality improvement project led and sponsored by the University of Southampton. All research measures will be self-administered on the web or by a paper questionnaire at the patient’s home or other locations of their choice. The staff will complete the measures at work or at a location of their choice. Data collection began when the first site opened on June 11, 2019**,** and continued until January 31, 2021. Clinics will join the study when appropriate local approvals are obtained; therefore, it is likely that the follow-up at each clinic will be for different durations.

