#### Patient Outcomes

##### Quantitative Measures

All data will be downloaded from the CHOICE web app, and patient use of all elements of CHOICE, including the hearing check, will be assessed. Errors in CHOICE, adverse events, and missed patient issues will be collected during the study period. Patients who take part in the focus group or interview will be asked to complete a short survey about the cost implications of switching to remote care (eg, impact on travel costs and need for childcare).

Quantitative data about patients’ use of CHOICE will be collected using the R-Outcomes survey tool [30]. These measures share a common framework with 4 items and 4 responses suitable for use on a mobile device and are validated, short, and have a lower reading age than other measures. R-Outcomes are incorporated into CHOICE and will assess the patients’ health, well-being, health confidence, digital readiness, and user experience. The NHS Friends and Family Test was also incorporated into the CHOICE web app, asking the question, “How likely are you to recommend this service to friends and family if they need similar care or treatment?” with 6 response options ranging from *extremely likely* to *extremely unlikely* [31].

We will use the following measures to assess empowerment, health-related quality of life, hearing, and patient care pathway preference: Patient Activation Measure (PAM), Cochlear Implant Empowerment Scale (CI-EMP), EuroQoL 5-Dimension 5-Level (EQ-5D-5L) questionnaire, Health Utilities Index Mark 3 (HUI3), a global change rating, and a discrete choice experiment (DCE). PAM is a well-validated generic measure of patient activation that evaluates the knowledge, skills, beliefs, and behaviors that patients have for self-management of their long-term condition [32,33]. The CI-EMP is a questionnaire specifically designed to measure how empowered people are to manage their own cochlear implant care [34]. The EQ-5D-5L is a standardized health outcome measure comprising five dimensions: mobility, self-care, usual activities, pain or discomfort, and anxiety or depression [35]. The HUI3 is a multi-attribute health status classification system that evaluates eight domains: vision, hearing, speech, ambulation, dexterity, emotion, cognition, and pain [36].

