#### Staff Outcomes

##### Quantitative Measures

CHOICE web app data about staff use of the clinician dashboard will be downloaded and analyzed. The staff will also be asked to complete the NHS Friends and Family Test and R-Outcomes (with additional measures of work well-being and innovation adoption) within the CHOICE clinician dashboard.

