#### Missing Data

We anticipate significant missing data because of the large number of outcomes measured and the clinical population. We expect that data will mostly be missing not at random, as those who discontinue the use of CHOICE or drop out are likely to be those who find it less helpful. This may lead to significant bias. There is likely to be a selection bias, as patients who agree to follow a remote care pathway may not be representative of the population. The same will apply to clinicians: those who want to be involved in implementing CHOICE are likely to be more invested in remote care than their colleagues. Following recommendations [42], when data are ready to be analyzed, inspection will suggest whether statistical methods should be used to handle missing data. As this is an outcome and process evaluation, the extent and pattern of missing data will in itself be significant, with nonresponse bias expected. It is also possible that reporting bias may occur; people with cochlear implants are often so grateful for their treatment that they may provide answers in the direction they perceive that the researchers want.

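### The only required post-baseline Friends and Family Test is tied to an undefined period of continued use, so the follow-up recommendation rate describes continuing users, not all users

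*Protocol article*

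**What the plan says.** Table 1 of the protocol article gives the NHS Friends and Family Test the same time point in its Patients and Staff parts: "Minimum of twice: baseline (on registration) and after using CHOICE for several months". In both rows the measure serves research question 1, the primary evaluation question on the impact of the rollout on users.

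The other patient questionnaires in that table (PAM and CI-EMP, global ratings of change, HUI3, EQ-5D-5L, discrete choice experiment) carry a different rule: "Baseline (on registration) and 6 months following registration or end of the project—whichever comes sooner".

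On delivery, Patient Outcomes, Quantitative Measures says "The NHS Friends and Family Test was also incorporated into the CHOICE web app". Staff Outcomes, Quantitative Measures places the staff version "within the CHOICE clinician dashboard". Project Design and Setting adds, in general terms, "All research measures will be self-administered on the web or by a paper questionnaire".

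On who will be lost, the Missing Data section says "We expect that data will mostly be missing not at random", and gives as the reason that "those who discontinue the use of CHOICE or drop out are likely to be those who find it less helpful". The Limitations section says that patients who stop will be asked why. No Friends and Family rating is scheduled at that contact.

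**The concern.** The second rating becomes due through use, not through calendar time. Someone who stops after a few weeks has not met the condition, and neither has someone who registers shortly before data collection closes. Both have a rating on registration, but that one precedes real experience of CHOICE. The ratings made after experience then come from people who stayed long enough.

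Primary question 1 is about the program's users, not those who persisted. If leavers are less favourable, as the protocol expects, the follow-up recommendation rate will look better than the view of all users. The Participants section says that an offer to all sites may depend on the evaluation results, and this rate is one of the measures behind them.

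**Working it through.** **Step 1. The two rules side by side (Table 1).**

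| | Friends and Family Test | PAM, CI-EMP, global ratings, HUI3, EQ-5D-5L, discrete choice experiment |
|---|---|---|
| First rating | On registration | On registration |
| Second rating counted from | Use of CHOICE | Registration |
| Length | Not defined | 6 months |
| Fallback at project end | None | Yes, if sooner |

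**Step 2. Who is never due a post-use rating.**

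- *Early leavers*: they do not reach the required period of use.
- *Late registrants*: recruitment and data collection both ran from June 11, 2019 to January 31, 2021 (Project Design and Setting; Recruitment). If the undefined period is read as 3 months (assumption), nobody registering after October 31, 2020 can qualify. Read as 6 months (assumption), the cut-off is July 31, 2020. The Limitations section itself expects many people to have used CHOICE only briefly by the close. The other questionnaires reach these people through the fallback.

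**Step 3. Size of the overstatement from early leavers.** The document gives no dropout rate and no recommendation rate, so there is no stated figure to reproduce. All inputs here are assumptions. Let *d* be the share who stop before the second rating, *s* the rate among stayers and *l* the rate leavers would have given.

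Rate among all = (1 − d)·s + d·l. Overstatement = s − rate among all = d·(s − l).

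Example: d = 0.30, s = 0.90, l = 0.60. Rate among all = 0.70 × 0.90 + 0.30 × 0.60 = 0.63 + 0.18 = 0.81. Overstatement = 90 − 81 = 9 points.

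| Stayers | Leavers | d = 10% | d = 30% | d = 50% |
|---|---|---|---|---|
| 90% | 80% | 1 | 3 | 5 |
| 90% | 60% | 3 | 9 | 15 |
| 90% | 40% | 5 | 15 | 25 |
| 80% | 80% | 0 | 0 | 0 |
| 80% | 60% | 2 | 6 | 10 |
| 80% | 40% | 4 | 12 | 20 |

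(Entries are percentage points.) The sign follows from the protocol's expectation about leavers. The document gives no such expectation about late registrants, so their absence narrows the group described without a known direction.

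**Step 4. Change from registration.** Suppose nobody changes their mind.

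- Everyone at baseline against stayers at follow-up, with leavers already lower at registration (90% and 60%, d = 30%): baseline 81%, follow-up 90%, an apparent rise of 9 points.
- The same comparison with leavers equal to stayers at registration (90% and 90%): no rise.
- People with both ratings only: no rise in either case, but the result describes stayers.

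**Step 5. What bounds would show.** With N registered, r rated and k recommending, the lower bound is k/N and the upper bound is (k + N − r)/N. For N = 100, r = 70, k = 63 (90% of raters): lower 63/100 = 63%, upper (63 + 30)/100 = 93%. The width, 30 points, equals the share without a rating.

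**The case against.** The strongest reply is that the protocol does not hide the problem. The Missing Data section expects discontinuers to be less favourable, warns of significant bias, and treats the pattern of missing data as a result in itself. Patients who stop are asked why. Asking for a recommendation after real experience is sensible, this is one of several measures for question 1, and the phrase may be only a rough follow-up time in a condensed table. This lowers the weight of the point. It does not remove it: disclosure does not correct a time point that builds in the selection when a better rule stands in the same table. When an outcome is collected is also protocol content, and here it is stated.

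Several stronger readings are tempting, and the documents do not support them.

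- *That leavers never rate CHOICE at all.* Everyone is due a rating on registration, and two is a minimum that allows more. Only a scheduled post-use rating is lacking.
- *That leavers would be invisible as missing data.* The registration rating supplies a known denominator, log-ins are recorded, and the Limitations section speaks of reporting dropouts.
- *That in-app delivery shuts out everyone who no longer logs in.* The general paper option may extend to this item; the text does not settle it. Paper would change the route, not the condition for being due.
- *That R-Outcomes has the same flaw.* The document says "R-Outcomes are incorporated into CHOICE", but Table 1 times those surveys from registration and every 6 months, so only ordinary non-response remains.
- *That the rate must rise even if no opinion changes.* This needs an unpaired comparison and leavers who were already lower at registration. The article fixes no such analysis; its denominators may be set in an analysis plan not shown.

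**Conclusion.** The point holds in limited form. In both Table 1 rows the only required post-baseline rating depends on an undefined period of use and has no project-end fallback. Read literally, early leavers and late registrants are never due one, and the follow-up rate answers a narrower question than primary question 1.

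The upward direction rests on the protocol's own expectation about those who discontinue. The size cannot be derived from the document: 0 points if leavers would rate as stayers do, and 25 points only if half stop early and the rates are 90% and 40%. None of these values is in the protocol. The flaw is worth correcting, but it affects one measure and does not touch the registration-timed questionnaires.

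**What to change.** *For further rollout.* In both Friends and Family rows of Table 1, use the time point that the other patient questionnaires already have, for all registered patients and staff: "Baseline (on registration) and 6 months following registration or end of the project—whichever comes sooner". The fallback must come with it, because a bare 6-month point would still miss late registrants. Also ask the item when patients who discontinue are asked for their reason. The cost is a wording change in two rows and one extra question at an existing contact. Ratings at project end will reflect unequal lengths of use, as they already do for the other questionnaires.

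*For the data already collected.* The Results section says that collection is complete and the research data are unanalyzed, so the remedy is in reporting:

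- give the follow-up rate with the number registered as denominator, for patients and staff separately;
- show how many left before rating and how many registered too late to rate;
- compare baseline with follow-up only in people with both ratings, and say that this describes continuing users;
- give two bounds, counting all non-raters first as not recommending and then as recommending.

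This needs no new data. The small downside is that the reported rate may be lower and less precise.

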The patient’s clinician at their cochlear implant center will have access to their results and web app use in the CHOICE web-based clinician dashboard. Cochlear implant center clinic appointments will be given if required, requested, or indicated by the outputs of the remote care tools. Otherwise, the patients in this pathway will continue with remote care. Participants may access the web app tools as often as they wish.

Automated flagging by email and website notifications will be the cornerstone of the remote care pathway. This will ensure that the patient’s problems are not missed and will provide the most efficient use of clinician time. Some patient flagging situations are as follows: no interaction with CHOICE for 3 months; hearing deterioration; patients who indicate that they need help on the general check-up questionnaire; each time a photo is uploaded, clinicians need to review it; replacement stock items are required; patient reports their daily sound processor use is **<**6 hours; request to leave CHOICE; and freedom of information request.

When an alert is received, the patient’s clinician will decide whether further action is required; for example, an in-center appointment.

The CHOICE website conforms to the following specifications: risk management (ISO 14971:2007) and software life cycle (BS EN 62304:2006) and complies with the requirements of the European Union directive 93/42/ECC for medical devices. It is Conformitè Europëenne marked and registered with the Medicines and Healthcare products Regulatory Agency as a Class 1 medical device.

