#### Quantitative

Descriptive statistics and graphs will be used to present the data. Data will be displayed visually wherever possible to facilitate sharing with various stakeholders. The significance value will be set at *P*=.05, including Bonferroni corrections for multiple comparisons where appropriate. All repeated-measures data will be compared at baseline and follow-up using analysis of variance to examine any changes in empowerment, hearing, and quality of life in the participants. Surveys will be analyzed at the baseline and follow-up time points using inferential statistical analyses. The choices of participants in the DCE will be subjected to conditional logit model analysis using the *survival* package of the R programming language.

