## Discussion

### Limitations

A total of 7 sites agreed to participate in the implementation and evaluation of CHOICE. These sites are mostly larger adult cochlear implant centers in England. Sites were self-selected: those participating were the centers that expressed interest in taking part. This means that it is unlikely that these centers are representative of all UK adult cochlear implant centers; they are likely to be more willing to innovate. Given that data collection will commence as soon as centers and patients join CHOICE, there will be variable periods of follow-up.

We expect significant effect modification in subgroups (eg, by age, gender, cochlear implant center, and other demographic factors). Assessing and reporting effect modifications may help identify a subset of patients who would not benefit from remote care. We attempted to control for confounding factors by collecting the demographic and digital readiness data. However, it is possible that there are confounders that remain unaccounted for; for example, we will not collect data on mental health and social support or the impact of the COVID-19 pandemic. It is likely that the concurrent COVID-19 pandemic will be the largest confounding factor in the data. In addition, the coincidental launch of a manufacturer-led remote care pathway (Cochlear Remote Check) for patients with some devices is likely to confound the results. The nature of recruitment for this study (cochlear implant center choosing to be involved and patient choosing to take part) means that there is likely to be a significant bias. Patients who choose to take part in a trial of remote care may not be representative of the broader population of people with cochlear implants. As recruitment is performed via patient and clinic choice, it is not valid to have a control group of people who do not follow a remote care pathway.

We are aiming for 6 months of follow-up data. This may be insufficient to highlight the benefits and limitations of remote care, especially in the climate of change because of the COVID-19 pandemic. In addition, as patients are encouraged to register for CHOICE at any point, there may only be a very short experience of using CHOICE by the end of data collection for many people.

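### Six patient instruments pool follow-ups of unequal length, because follow-up stops at project end and recruitment stays open to that same day; the result is not a 6-month change

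*Protocol article*

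**What the plan says.** In the protocol article, the Patients block of Table 1 gives six instruments a baseline at registration and a second measurement at "6 months following registration or end of the project—whichever comes sooner". They are PAM, CI-EMP, the global ratings of change, HUI3, EQ-5D-5L and the discrete choice experiment (DCE).

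On dates, Project Design and Setting states "Data collection began when the first site opened on June 11, 2019" and then "and continued until January 31, 2021. Clinics will join the study when appropriate local approvals are obtained". The Recruitment section gives the same closing day for enrolment: "and continued until January 31, 2021".

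On analysis, Data Analysis, Quantitative, states "All repeated-measures data will be compared at baseline and follow-up using analysis of variance", to examine change in empowerment, hearing and quality of life. It gives no follow-up window, minimum exposure or term for length of follow-up. DCE choices go to a conditional logit model instead.

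Limitations gives 6 months of follow-up as the aim and concedes that "there may only be a very short experience of using CHOICE by the end of data collection for many people".

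Home hearing checks are listed in Table 1 as all data, without a follow-up time point. Intervention adds: "Participants may access the web app tools as often as they wish".

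**The concern.** The timing rule and the two-level comparison are both stated, and together they settle what is estimated. A patient who registers late in the window and fills in a second form at project end contributes a follow-up value of the same standing as a patient measured at 6 months. The average change then refers to a mixture of exposures whose composition depends on the accrual curve, and not to the 6 months that Limitations gives as the aim.

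This matters most for the second primary research question, which asks for a gain in empowerment together with no harm to hearing and quality of life. If change accumulates with use, short follow-ups shrink both parts. A smaller empowerment gain is harder to show. A smaller loss of quality of life or HUI3-rated hearing is easier to miss, and so easier to report as no harm.

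The home hearing check raises a different problem. The analysis section applies the same baseline versus follow-up comparison to hearing. The Intervention section describes a baseline check, but nothing says which later check, or what summary of later checks, is the follow-up.

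**Working it through.** The article gives no power, effect size or formal sample size bearing on this point, so there is no stated figure to reproduce. The check is date arithmetic plus assumed accrual patterns.

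**Inputs from the article.** Start 11 June 2019; end of data collection and of recruitment 31 January 2021; planned follow-up 6 months.

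**Assumptions.** The article does not date the end of the project; it is taken as 31 January 2021. No accrual curve is given, so cumulative accrual is set to F(t) = (t/D)^k, with k = 0.5 (front-loaded), 1 (uniform), and 2 and 3 (accrual rising over time). All registrants are assumed equally likely to return a second form, on the day it falls due.

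**Step 1: window.** D = 600 days (19.7 months). Six months is m = 182.6 days, so m/D = 0.304. The last calendar date allowing 6 months is 31 July 2020.

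**Step 2: share who cannot reach 6 months.** This is 1 − (1 − m/D)^k. Uniform: 1 − 0.696 = 0.304. For k = 2: 1 − 0.696² = 0.516. The same formula with m/2 and m/6 gives the shares under 3 months and under 1 month.

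**Step 3: share of the 6-month change retained.** If change grows linearly to 6 months, each patient contributes min(time to project end, m)/m. The mean is D/[m(k+1)] × [1 − (1 − m/D)^(k+1)]. Uniform: 600/(2 × 182.6) × (1 − 0.696²) = 1.643 × 0.516 = 0.848.

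| Accrual | Under 6 months | Under 3 months | Under 1 month | Mean follow-up (months) | Retained, linear | Retained, plateau at 3 months |
|---|---|---|---|---|---|---|
| k = 0.5 | 17% | 8% | 3% | 5.5 | 92% | 96% |
| k = 1 | 30% | 15% | 5% | 5.1 | 85% | 92% |
| k = 2 | 52% | 28% | 10% | 4.4 | 73% | 86% |
| k = 3 | 66% | 39% | 15% | 3.8 | 63% | 79% |

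If the effect is immediate, 100% is retained under every pattern.

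**Step 4: which outcomes this covers.** The cut-off rule applies to the six instruments above. The ANOVA dilution concerns those that enter the baseline versus follow-up comparison. The DCE shares the mixed timing but has its own model. R-Outcomes are repeated every 6 months, the Friends and Family Test comes after several months of use, and service outcomes are aggregate activity before and after introduction. None of these is under the rule. Home hearing checks are not under it either, so Steps 2 and 3 say nothing about their dilution; their problem is the undefined follow-up check.

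**The case against.** The case on the other side has several parts.

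- **The article discloses the problem.** Variable and very short follow-up are conceded, and the project was not set up to test a hypothesis formally. Visit windows and analysis sets are often left to a fuller plan. That lowers the severity. But the article does state the timing rule and the comparison, and a limitation paragraph does not change what they estimate.
- **A reader might infer that all changes are pulled toward zero.** The documents do not support this. The rule covers six instruments. Attenuation needs change that builds with exposure, and no time course is given. The article itself expects grateful reporting and names the pandemic as the likely largest confounder; these, and regression to the mean, can move changes in either direction.
- **A reader might infer that many patients with almost no exposure count as followed up.** Under uniform accrual about 5% have less than 1 month (3% to 15% over the patterns). They enter the comparison only if they return a second form, and Missing Data expects substantial non-return.
- **A reader might infer that late site opening makes heavy late accrual likely.** The article says only that clinics join once approvals are in place and that durations will differ. Front-loaded accrual is equally compatible with it, so the range must include it.
- **An analysis limited to completed 6-month follow-ups has its own bias.** Missing Data expects those who drop out to be those who found CHOICE less helpful, so selecting completers may flatter it. This stands and shapes the fix. So does the point that short exposure on the questionnaires is tied to late registration and pandemic timing, which a model cannot separate.

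**Conclusion.** The point holds in limited form. As written, the plan pools unequal follow-up on six instruments, and for those in the ANOVA the pooled change is not a 6-month change, whatever the shape of the effect. With 31 January 2021 as project end, about 30% of registrants cannot reach 6 months under uniform accrual (17% to 66% over the assumed patterns).

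The direction and size of any bias are conditional. With linear growth to 6 months and equal return of forms, 85% of the 6-month change is retained under uniform accrual (63% to 92%), a shrinkage of 8% to 37%. With an immediate effect there is none. Where dilution occurs, it acts against the empowerment half of the second primary question and in favour of the no-harm half, for quality of life and HUI3-rated hearing.

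The missing definition of a follow-up home hearing check is a separate gap and needs none of these assumptions. Both are inexpensive to correct and worth correcting before analysis; neither invalidates the project.

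**What to change.** 1. Make the 6-month analysis of the second primary question the patients registered by 31 July 2020. Define the set by registration date, not by completion. Report how many lack a follow-up and how they differ at baseline from those who have one.
2. Report the truncated end-of-project follow-ups separately, by duration.
3. As the all-patient analysis, replace the two-level ANOVA with a linear mixed model on actual time since registration, and report the estimated change at 6 months. For hearing, use every home hearing check in this model, which also settles the undefined follow-up check.
4. State with that model that short exposure is confounded with late registration and pandemic timing, and that its usual missing-at-random assumption conflicts with the article's expectation of data missing not at random.

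**Cost.** A change of analysis wording and no new outcome data; the Results section says the research data had not yet been analysed. Registration dates already drive the 6-month schedule. Completion dates are also needed, and the article does not say they are recorded for paper forms, so this should be confirmed. The price is fewer patients and less precision in the 6-month analysis: about 30% fewer registrants under uniform accrual, 17% to 66% over the assumed patterns.
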